### Training procedure: participants’ journey

Participating nurses will be released from their working shift for two hours in order to attend the assigned simulation program at their place of work. The procedures for Group 1 web-based intervention and Group 2 face-to-face simulation journey are summarised in Table 1. For Group 2, participants will work in teams of three with a patient actor and research ‘support’ staff; thus over an 8-h shift 12 nurses will complete the training. This release will be enabled by the rostering of additional senior nursing staff as backfill on training days. For Group 1, web-based training will be completed individually on a personal computer or in a ward training room.

**Table 1 Tab1:** Flow chart of participants’ journey in web-based simulation and face-to-face high fidelity clinical learning environment scenarios

	Group 1	Group 2
	FIRST^2^ACT Web	FIRST^2^ACT In-situ face-to-face
Introductory preamble	Short written introduction with explanation.	Short verbal introduction with explanation.
Demographics and Pre-course MCQ	A demographics form and an 12-item multiple choice questionnaire (MCQ).	As in web-based.
Background material	An animated slide show – with voice over from an educator.	As in web-based.
Scenarios	Scenario (i) – Cardiac scenario Scenario (ii) – Shock scenario Scenario (iii) – Respiratory scenario Total score and feedback provided. Each scenario runs for 8 min with acute deterioration at the mid-point.	As in web–based. Video recorded scenarios are rated by attending researchers.
Feedback	The software gathers all performance data for automated feedback at the end of each scenario.	Face-to-face feedback will be conducted with an educator using video and performance records.
Post-course MCQ	Repeat of the MCQ.	As in web-based.
Course evaluation	A course evaluation and reflective review of educational impact	As in web-based.
Certification	Download a course participation certificate	Issued with a course participation certificate.
Course Manual	Download the course manual for reflection and review	Issued with the course manual for reflection and review
Time commitment	1.5 h	2 h

Described in full below, quantitative data will be captured from the following sources:Patient medical records.A multiple choice knowledge questionnaire (MCQ).Standardized performance measurement forms.Participant evaluations.Costs derived from patient records and inventory of resources.

Qualitative data will be captured in six stakeholder focus groups (three at each site) at the end of the study. Participants will include those who attended training and their line managers in order to elicit the impact of the two programs of education.

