#### Knowledge and skill performance ratings

Participant demographics, questionnaire, and simulation performance will be described with the use of descriptive and inferential statistics. Measures of dispersion (means, medians, etc.) will be reported. There will be a range of nominal, ordinal and interval data (paired and unpaired) requiring tests such as Chi-square; McNemar; Mann Whitney U; and t-tests. Multivariate analysis (linear and logistic regression) will be used to identify predictors of performance. Simulation exercises will be rated by two researchers for inter-rater reliability. A significance level of *p* < .05 will be applied throughout.

Based upon a Generic Qualitative Design eight stakeholder focus groups will be completed (two at each site) in order to identify the perceived impact of the program(s) [52]. Core themes and outcomes will be identified using Miles and Huberman’s stages of data analysis [53]. Analysts will attribute nominal codes to narrative segments and group narrative segments to identify key themes. Emergent themes will be shared and collaboratively refined to achieve a consensus for reporting. The reporting of findings will by guided by the COREQ guidelines for reporting qualitative research.

The program is designed to run for 18 months with a seven month lead-in, to enable literature reviews, ethical approval, access arrangements and refinement of data collection tools. The training intervention will be compressed into a four month period and subsequent patient notes review, data analyses and report writing will take a further seven months.

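### Face-to-face nurses perform in teams of three, but the named tests for simulation performance treat nurses as independent and do not keep the two programs' differently captured scores apart (minor)

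*Protocol article*

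**What the plan says.** The Training procedure section of the protocol article gives the two programs different units of delivery. For face-to-face: "For Group 2, participants will work in teams of three with a patient actor", and "thus over an 8-h shift 12 nurses will complete the training". For web: "For Group 1, web-based training will be completed individually on a personal computer or in a ward training room".

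Scores also arise differently. In Table 1 the web entry reads "The software gathers all performance data for automated feedback at the end of each scenario", while the face-to-face entry reads "Video recorded scenarios are rated by attending researchers". The article does not say whether a face-to-face rating belongs to one nurse or to the team.

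Under Data analysis, the subsection Knowledge and skill performance ratings puts demographics, questionnaire and simulation performance under one plan. It describes the data as "requiring tests such as Chi-square; McNemar; Mann Whitney U; and t-tests" and adds: "Multivariate analysis (linear and logistic regression) will be used to identify predictors of performance". A 5 % significance level applies throughout. The subsection names no team term and does not split the analysis by program.

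On comparing the programs, two sections pull apart. Methods/design announces comparisons both inside each group and across the two groups. The Discussion says the two versions are not to be compared directly, because they are delivered so differently.

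**The concern.** Three nurses who manage the same patient actor in the same eight-minute scenario may receive one common rating, or three ratings that resemble one another. Either way, they carry less information than three nurses scored alone. Chi-square, Mann-Whitney, t-tests and ordinary regression count each nurse as a separate observation, and McNemar counts each nurse's pair as one. Used as named, they would give standard errors that are too small for anything that does not vary within a team, such as program, site or training day.

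A second issue is one of bias rather than precision. Software capture of web actions and researcher ratings of video may not be on the same scale. If both enter one model of performance, a difference in scoring method could be read as a difference in skill.

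At stake are claims about which factors go with better simulation performance, and any performance contrast between the programs.

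**Working it through.** **Inputs from the article.** Team size is 3 in Group 2 and 1 in Group 1. The significance level is 5 %, taken as two-sided because the article does not say. About 160 nurses are employed at the larger hospitals and 85 at the other two sites, with 82 % participation expected.

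**Reproducing the article's own figures.**
- Nurses: (160 + 85) × 0.82 = 200.9, which agrees with the stated sample of more than 200.
- Throughput: (8 h / 2 h per session) × 3 = 12 per shift, which agrees and confirms the team as the unit of delivery.

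**Assumptions.** Half of about 200 nurses are in Group 2: about 100, or about 33 teams. The article gives no within-team correlation ρ, so a range is shown; ρ = 1 means one score shared by the team.

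**Formulas.**
- Within Group 2, for a factor constant within a team: design effect DE = 1 + (3 − 1)ρ = 1 + 2ρ.
- Web versus face-to-face, with equal numbers and variances and only Group 2 clustered: DE = (1 + 1 + 2ρ)/2 = 1 + ρ.
- True size of a nominal 5 % test = 2[1 − Φ(1.96/√DE)].
- Effective Group 2 sample = 100/(1 + 2ρ).

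Example at ρ = 0.5: the within-group DE is 2.0, the standard error should be √2 = 1.41 times the naive one, and 2[1 − Φ(1.96/1.414)] = 0.166.

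| ρ | DE within Group 2 | SE factor | True size | Effective n | DE web vs face-to-face | True size |
|---|---|---|---|---|---|---|
| 0 | 1.0 | 1.00 | 0.050 | 100 | 1.0 | 0.050 |
| 0.1 | 1.2 | 1.10 | 0.074 | 83 | 1.1 | 0.062 |
| 0.3 | 1.6 | 1.26 | 0.121 | 63 | 1.3 | 0.086 |
| 0.5 | 2.0 | 1.41 | 0.166 | 50 | 1.5 | 0.110 |
| 1.0 | 3.0 | 1.73 | 0.258 | 33 | 2.0 | 0.166 |

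**Check by simulation** (20,000 runs, 33 teams of 3 against 99 individuals, t-tests). At ρ = 0.1, 0.3, 0.5 and 1.0 the rejection rates were 0.071, 0.124, 0.170 and 0.262 for a test on the Group 2 mean, and 0.061, 0.084, 0.113 and 0.168 between programs. At ρ = 0 both were about 0.05.

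**Predictors that vary within a team.** The approximate design effect is 1 + 2 × ρ(outcome) × ρ(predictor). If a predictor such as years of experience or questionnaire score is unrelated among team-mates, this is 1 and the test keeps its size. With ρ(outcome) = 0.5 and ρ(predictor) = 0.1 it is 1 + 2 × 0.05 = 1.1, a true size of about 0.062.

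These figures count team clustering only and take no account of any further correlation by hospital.

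**The case against.** The strongest reply is that the premise is not in the article. It never says that a rating is shared by the team, and the section on skill performance speaks of all participants completing the exercises. It gives no correlation, and at ρ = 0 nothing is wrong. The list of tests is open and is not assigned outcome by outcome. Regression does not exclude a team term, and a fuller analysis plan may supply one. This stands as far as it goes: the understated error is conditional. It does not remove the point, because the article chose to name its methods and in standard form they do not match the team delivery it also fixes. Zero correlation among three people handling one scenario together would be surprising.

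A reader might infer that every performance analysis could have an error rate of up to 26 %. The documents do not support that. The figure needs a shared score and a factor constant within Group 2 teams. A program contrast is diluted by the unclustered web group, and many natural predictors vary between team-mates.

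A reader might also infer that the plan pools the two programs. It does not say so, and the Discussion disclaims direct comparison. But the analysis section sets no such limit, and Methods/design speaks of comparing across groups. Nor is it settled that the scoring differs throughout: the analysis section has two researchers rating the simulation exercises without confining this to Group 2. Non-comparability is therefore a risk, not an established fact.

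**Conclusion.** The concern holds in conditional form and is minor. If Group 2 scores are shared or correlated within teams, the named methods understate uncertainty for team-constant factors. The true size of a nominal 5 % test is about 7 to 26 % within Group 2 and about 6 to 17 % between programs, over correlations of 0.1 to 1.0. This rests on an assumed 100 Group 2 nurses in teams of exactly three, equal group sizes and variances, and two-sided testing. The sizes depend on the team size and the correlation; the assumed 100 nurses drive the effective sample size.

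The difference in score capture is a separate comparability problem. It matters only if scores from both programs are modelled or compared together.

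A reader might conclude that the trial's main findings are at risk. They are not. The primary outcomes (late signs of deterioration and quality of nursing assessment) come from patient records. The secondary outcomes are costs, stakeholder views, mortality and ICU admission. Simulation performance is in neither list, and the knowledge questionnaire is not a team-scored exercise.

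**What to change.** 1. Record a team identifier for every Group 2 nurse, and state whether the face-to-face score is given per nurse or per team.
2. If it is per team, analyse one score per team per scenario, allowing for the three scenarios that each team completes. If it is per nurse, use a random team effect or standard errors clustered on team.
3. Fit performance models separately for the web and face-to-face programs, in line with the Discussion, and reconcile Methods/design with it.

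The cost is small: one extra variable and a changed model, with no additional participants. Data collection was already under way when the article was written, so the identifier may have to be recovered from the scenario videos for sessions already held. The downside is wider confidence intervals for team-level factors in Group 2. At a correlation of 0.3, for example, they would be about 1.26 times as wide as the naive ones.

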### Data collection tools

#### Patient medical records review

Using patients’ demography, diagnoses and vital signs data, outcomes will be measured in relation to deterioration including ICU admissions and mortality rates, etc. Further, based on our sample size calculations and the guidance produced by Harrison et al. [38], McQuillan [39] and NICE [40] we aim to identify a change in patient management by measuring the applicability of physiological observations, actions in relation to deterioration, and early and late signs of deterioration to identify improvements in performance (Table 2). We have developed and tested a chart audit tool based on a rationale for item inclusion, definitions, and clinical expert ratings of relevance and clarity with a high Content Validity Index of 0.83 [41]. We will therefore extract data from patient records from 80 randomly selected cases from each month, three months before the simulation intervention, and from each month for three months after the intervention (total *n* = 480 at each site). A post-hoc sensitivity analysis will be conducted to assess the representative nature of the sample.

**Table 2 Tab2:** Early and late signs of patient deterioration [Adapted from Harrison et al. [38]

Parameter	Early signs	Late signs
Oxygen saturation	90–95 %	<90 %
Systolic blood pressure (mmHg)	80–100 or 181–240	<80 or >240
Heart rate	40–49 or 121–140	<40 or >140
Respiratory rate	5–9 or 31–40	<5 or >40
Glasgow coma scale	N/A	>2 point drop

### Intervention measures

#### Knowledge

A validated Multiple Choice Questionnaire (pre-post) [42–44] will be completed by participants before and after the program in order to measure patient deterioration knowledge. This measure will enable identification of knowledge in relation to skill performance and changes in knowledge based on program participation.

#### Skill performance measurements

All participants will complete three contrasting simulation exercises that are either recorded as interactive web-based versions or completed face-to-face with a patient actor. Each scenario will be based on common presenting conditions (e.g. acute myocardial infarction, shock and a respiratory case). Standardized patients (actors) will simulate the clinical scenarios. During the simulation exercises, information will be presented in a manner that most clearly reflects the real world requiring participants to be an active searcher [45]. This approach will enhance the ecological validity of the simulation [46] allowing the participant to experience clinical thinking in a more dynamic manner. Levels of relevant information and levels of uncertainty will be taken into account [47] and incorporated into the scenarios.

#### Debriefing and feedback

The web-based version collects performance data for feedback at the end of each scenario, producing a score and written feedback. In the face-to-face version a video recording of the participants’ performance during the simulation exercise enables comprehensive verbal feedback. Written participant evaluations will be sought by survey after the training activities as an evaluation of the educational impact of each program.

### Economic analysis

We will conduct a cost analysis [48, 49] to assess total costs of training. The primary outcome of the cost analysis will be comparison of total costs between web-based versus face-to-face simulation education interventions. Secondary outcomes will include comparison of the costs associated with each intervention (e.g. software development, educator staffing costs, staff release costs, patient actors, etc.). In addition, hospitalization costs will be estimated using the Australian Refined Diagnosis Related Groups (AR-DRGs, Version 7) [50, 51] model, adjusting for ICU admissions and mortality.

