### Aim and hypothesis

This research aims to measure the impact of two forms of simulation education on nurses’ ability to detect and manage patient deterioration, to assess patient outcomes and to compare the total costs between the two interventions. The research hypotheses to be tested are:(i).Both the face-to-face and web-based models of simulation education will improve the detection and management of patient deterioration and patient outcomes.(ii).The web-based program will have lower total costs in improving the detection and management of patient deterioration and patient outcomes.

The primary outcomes to be measured are the proportion of patients showing late clinical signs of deterioration, and the quality of nursing assessment. The secondary outcomes to be measured are the cost of provision of face-to-face versus web-based training, together with stakeholders’ views and attitudes regarding the forms of program delivery, and change to in-hospital mortality and the rate of admission to ICU (see Fig. 1).

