### Sample selection and recruitment

#### Participants

Registered nurses will be recruited from a medical ward in one of four Victorian acute care hospitals. Both Division 1 Registered nurses and Enrolled nurses will be included. Two medical wards will be assigned as Group 1 (web-based intervention), while another two will be assigned as Group 2 (face-to-face intervention). This approach ensures that there is no contamination between homogeneous groups. There are approximately 160 nurses employed at the larger hospitals and 85 at the remaining two sites. In pilot hospital-based studies we have achieved a participation rate of 82 % and anticipate similar participation for this study (*n* = >200). Maximising staff attendance is important in order to have the greatest effect on clinical outcomes.

Nurses in each group will be recruited by a member of the research team who will provide a brief explanation of the study and invite nurses to participate in the study. Participant information sheets and consent forms will be made available and written consent obtained.

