## Discussion

This project will add to the body of knowledge in relation to the ‘failure to rescue’ literature with a concern for measuring and improving the management of deteriorating patients. This is a contemporary international issue and one that the project funder – The Victorian Government – is keen to address.

In this mixed methods interventional trial we will investigate the clinical and financial impact of two forms of simulation education. Whilst many studies have identified the educational impact of simulation approaches few have identified how such approaches impact on clinical care and patient outcomes in combination with a cost benefit analyses. Importantly, the reader should note here that it is our intention to compare program *impact* rather than draw direct comparisons between the web-based and face-to-face versions of the program, as they are quite different forms of delivery.

In testing educational interventions Sullivan [54] suggests that there is a need to understand practice and patient safety issues in the real world through ‘pragmatic trials’. These may be cross sectional studies (data from a specified time), longitudinal approaches (exposures over time), cluster randomised trials, quasi (non-randomised) experimental approaches or a range of mixed methods approaches [55]. Individual randomisation of subjects in education trials is problematic as cross-contamination is likely, the dynamics within existing groups will be changed and ethical concerns are raised when individuals are given no choice relating to learning methods [56]. Further, control of such trials is difficult as educational delivery style will differ, participants will attend at different times, and comparison groups are often dissimilar (e.g. comparing lectures with simulation). Randomisation is therefore not the gold standard in education [54, 55].

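### The primary cost outcome is an unscaled total, so it mixes the price of each program with the number of nurses each group trains

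*Protocol article*

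**What the plan says.** Hypothesis (ii), under Aim and hypothesis, reads: "The web-based program will have lower total costs in improving the detection and management of patient deterioration and patient outcomes". The Economic analysis section sets out a cost analysis "to assess total costs of training" and names its lead measure: "The primary outcome of the cost analysis will be comparison of total costs between web-based versus face-to-face simulation education interventions". Its secondary outcomes are the component costs, with software development, educators, staff release and patient actors as examples. No cost per nurse, per ward or per unit of effect is defined.

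On volume, the Participants section says: "There are approximately 160 nurses employed at the larger hospitals and 85 at the remaining two sites". It expects 82 % participation and more than 200 nurses. It assigns two wards to each program but does not say how larger and smaller hospitals are paired.

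On time, the training procedure section says of both groups: "Participating nurses will be released from their working shift for two hours". In Table 1 of that section, the row "Time commitment" gives 1.5 h for the web program and 2 h for face-to-face.

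Hospitalization costs are a further analysis. They are estimated from diagnosis-related groups, "adjusting for ICU admissions and mortality". The Background announces a cost benefit analysis, a term that the Economic analysis section does not use.

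**The concern.** Total cost is a fixed part plus a cost per nurse multiplied by the number of nurses. Hypothesis (ii) is about which mode of delivery is cheaper, so the relevant quantities are the fixed part and the cost per nurse. The number trained depends on which hospitals were placed in which group and on local uptake. An unscaled total carries that number straight into the comparison.

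This matters because the cost hypothesis is one of only two in the study, and a hospital deciding between programs will apply the result to its own staff numbers. A difference in totals from groups of unequal size does not transfer to another hospital.

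The release time has a similar effect on a smaller scale. Staff release is a named cost item, and the article does not say whether the web group is costed at its two-hour release or at its 1.5 h program time.

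**Working it through.** **Inputs.** Nurse pools of 160 and 85, 82 % participation, and an expected sample above 200 (Participants). Release of 2 h for all, program time of 1.5 h web and 2 h face-to-face, and 12 nurses trained face-to-face per 8-h shift (training procedure and Table 1).

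**Reproducing the plan's figure.** (160 + 85) × 0.82 = 200.9, which agrees with the stated sample above 200. This reads 160 and 85 as totals over two hospitals each. Read as figures per hospital, the expected number would be 490 × 0.82 = 402, a poor fit. The ratio of large to small pool is the same under either reading.

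**Range of group sizes.** Assume equal participation everywhere and an even split within each pair of hospitals.
- Two larger sites: 160 × 0.82 = 131.2 nurses.
- Two smaller sites: 85 × 0.82 = 69.7 nurses.
- One larger and one smaller site: 200.9 / 2 = 100.5 nurses.
- Largest ratio between groups: 131.2 / 69.7 = 1.88.

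**Effect on the total.** Write total cost as F + N × v, with F fixed, N nurses and v variable cost per nurse. If v is the same in both programs, the variable parts stand in the ratio of the two N, so between 0.53 and 1.88 (69.7 / 131.2 = 0.53). With both larger sites in the face-to-face group, the web program could cost almost 1.88 times as much per nurse in variable cost and still show the lower variable total.

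**Release hours, the one item the article lets us count.**

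| Pairing | Nurses, web : face-to-face | Web hours at 1.5 h / 2 h | Face-to-face hours at 2 h | Ratio web / face-to-face |
|---|---|---|---|---|
| One larger, one smaller site each | 100 : 100 | 151 / 201 | 201 | 0.75 / 1.00 |
| Both larger sites web | 131 : 70 | 197 / 262 | 139 | 1.41 / 1.88 |
| Both larger sites face-to-face | 70 : 131 | 105 / 139 | 262 | 0.40 / 0.53 |

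In the second row the web group uses more release hours in total, although no nurse in it spends longer than a face-to-face nurse.

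**Face-to-face delivery.** At 12 nurses per shift the number of training shifts would be 69.7 / 12 = 5.8 (6 shifts), 100.5 / 12 = 8.4 (9 shifts) or 131.2 / 12 = 10.9 (11 shifts). Educator and actor costs would follow that count.

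**Release time.** Per nurse, (2 − 1.5) / 2 = 25 % saving for web if program time is costed, and zero if the two-hour release is costed.

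**The case against.** The strongest reply is that imbalance is possible but not shown. The article is silent on pairing, and a condensed article's silence is not evidence that sizes are unequal. With one larger and one smaller site per group, headcount is about equal and the total is a fair comparison. This stands: 1.88 is the extreme case, and it applies to variable costs only.

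A second reply is that the planned component costs, divided by the number of nurses, would give unit costs anyway. That is true, but they are secondary, and the result declared for hypothesis (ii) would still rest on the total. It can also be said that cost per nurse depends on headcount once fixed software cost is spread over it. That is correct, and it is why fixed and variable costs need to be shown apart.

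Four stronger readings are tempting, and the documents do not support them.
- A reader might infer that site pairing alone could reverse the verdict on total cost. The reversal above is in release hours. The article gives no prices, actors and attending staff belong to the face-to-face program, and software is a fixed cost, so a reversal of total cost is not demonstrated.
- A reader might infer that the web release time is stated twice with different values. Release is stated once, as two hours. The 1.5 h is a time commitment, and a nurse can be released for longer than the program takes. What is unclear is which time is costed.
- A reader might infer that "adjusting for ICU admissions and mortality" means covariate adjustment, which would remove part of any effect of training on cost. It may equally mean adding the cost of ICU stay or death to the estimate. This analysis is also separate from the training total that forms the primary cost outcome.
- A reader might take "in combination with a cost benefit analyses" in the Discussion as a commitment. That sentence describes what few earlier studies have done. Only the Background announces such an analysis for this study.

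The Discussion also says that the two versions are not meant to be compared directly. Hypothesis (ii) and the primary cost outcome nevertheless compare their costs directly, so the scale of that comparison still matters.

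**Conclusion.** The concern holds in a limited form. The article fixes an unscaled total as the primary cost outcome while leaving the number of nurses per group open. Under its own figures, headcount could range from about 100 and 100 to 131 and 70, so volume-driven costs could differ up to 1.88-fold at identical cost per nurse. This rests on 160 and 85 being totals per pair of hospitals (the ratio does not depend on it) and on equal participation across sites. With one larger and one smaller site in each group, the problem is small. How far the overall total would move cannot be stated without prices.

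The costed release time is a second open input, worth 25 % or nothing of web release cost per nurse. The wording on ICU admission and death, and the mismatch of terms between Background and Economic analysis, are minor points of clarification.

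**What to change.** - Make cost per nurse trained the primary cost comparison for hypothesis (ii). Show fixed costs (software development) and variable costs (release, educators, actors) separately for each program, with the number of nurses trained, and keep totals as secondary.
- State which hospitals are in which group.
- Cost the release hours actually used in each group, and reconcile the two-hour release with the 1.5 h web time commitment in Table 1.
- State that ICU admission and death enter hospitalization cost as cost components and are not covariates, because both are outcomes of the trial.
- Align the Background's cost benefit term with the cost analysis that is actually specified.

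The change is mainly one of analysis wording. The inventory of resources and the patient records are already planned data sources, although release hours would have to be among the items logged. The price is that the headline becomes a unit cost, accompanied by a fixed cost, and is no longer a single total.
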